#### Additional analyses

Factors associated with an improved treatment response will be assessed to see whether a particular patient population is more likely to have a positive response. The distribution of risk factors for poor outcome after knee replacement according to the CORKA screening tool will also be investigated.

For the subgroup of patients who provide 2 year follow-up data, methods previously described to analyse the data from each questionnaire will be repeated incorporating this measurement.

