#### Secondary outcomes

The secondary outcome measures, recorded at 6 and 12 months post-randomisation, are as follows:LLFDI frequency and limitation total dimension scores: 16-item patient reported outcome measures (PROMs), each with a total score ranging from 0 to 100, with higher scores indicating higher levels of frequency of participation in life tasks and capability of participation in life tasks respectively.The Oxford Knee Score (OKS) [12]: a 12-item PROM with total scores ranging from 0 (most severe symptoms) to 48 (least severe symptoms).The Knee injury and Osteoarthritis Outcome Score (KOOS) quality of life subscale [13]: four self-reported questions with total scores ranging from 0 (extreme problems) to 100 (no problems)The Physical Activity Scale for the Elderly (PASE) questionnaire [14]: a 12-item, self-reported measure. The time spent participating in each activity is multiplied by a weight corresponding to that activity, and these weighted values are summed to calculate total PASE scores, with higher scores indicating greater levels of physical activity.Health economics using the EuroQol EQ-5D-5L [15]: a self-reported outcome measure consisting of 5 dimensions each with 5 possible responses which are converted to multi-attribute utility scores, where 1 represents perfect health, 0 represents death, and scores less than 0, representing a quality of life worse than death, are possible.Measurement of physical function using the 30-s chair stand test, the figure of 8 walking test, and the single-leg stance test.

For the subgroup of patients who reach 2 years post-randomisation prior to the end of the trial, questionnaire data will be collected at this time point. This will include the LLFDI overall function score, and frequency and limitation total dimension scores, the OKS, the KOOS quality of life subscale, the PASE, and the EuroQol EQ-5D-5 L.

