### Statistical analysis

#### General analysis principles

Two analysis populations will be considered: (1) the intention-to-treat (ITT) population; and, (2) the per-protocol (PP) population. The ITT population will include all randomised participants analysed according to the intervention to which they were randomised. The ITT population will be the primary analysis set, and all analyses will be conducted for this population if not otherwise stated. Analyses on this population provide an estimate of the effect of treatment offer.

The PP population will be analysed according to the intervention they actually received. Participants with major protocol deviations or violations, that is, those who did not receive treatment or did not provide any follow-up data, will be excluded from the PP population. The definition of the PP population will be finalised by the trial statistician during a blinded analysis of the data (i.e. without details of treatment allocation) prior to the primary analysis time point; any unanticipated protocol deviations which occur will be identified at this point. Analysis of the PP population will be conducted as sensitivity analyses for important outcomes and will address the effect of the intervention in those who receive it and provide follow-up data.

The significance level used throughout will be 0.05, and 95% confidence intervals will be reported. The primary conclusion of the trial will be based on the results from the primary analysis of the primary outcome, and all secondary analyses will be considered as being supportive of the primary results.

All analyses will be carried out using appropriate, validated statistical software such as Stata [17] or R [18]. The relevant package and version number used for the analysis will be recorded and reported.

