#### Analysis of primary outcome

The LLFDI at 12 months will be summarised by treatment arm using means and standard deviations and analysed using a linear mixed effects model with repeated measures incorporating outcome measurements at 6 and 12 months and adjusting for baseline score and study site as covariates. An interaction between outcome measurement time point and randomised group will be fitted to allow estimation of the treatment effect at each time point, reported as the adjusted mean difference in LLFDI between groups at 12 months along with the standard deviation of this difference; the treatment effect at 12 months will be considered the primary endpoint. The distribution of the change from baseline will be assessed for evidence of departure from normality using residual plots. If necessary, data will either be transformed to achieve normality or analysed using a non-parametric equivalent.

Steps will be taken to minimise missing data, including repeated efforts by the trial team to contact those who do not return for their 12 month appointment; however, there will inevitably be some missing data either in the form of total non-response post-randomisation or item non-response. Missing data will be reported for both types of non-response, and reasons for the non-response will be provided. The missing data pattern will be explored. In order to be consistent with the ITT principle, missing data will be imputed using multiple imputation (MI) techniques [22]. The imputation model used will include all variables used in the analysis model (baseline score and study site) as well as any other important factors believed to predict the outcome or missingness. This judgement will be based on visual assessment and clinical opinion and will improve the validity of the imputation model under the missing at random (MAR) assumption. Imputation will be performed separately for each treatment group, and the number of replicates will be equal to the proportion of missing data [23]. Deviations from the MAR assumptions will be explored by repeating the MI under different assumptions as part of the sensitivity analyses. In the unlikely event of a large number of missing data points for a variable in the primary outcome analysis, an alternative method will be considered during the blinded analysis, as MI is not suitable in this case.

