#### Analysis of secondary outcomes

The LLFDI frequency and limitation total domain scores will be analysed using the methods described for the primary outcome.

If the assumption of normality holds, other continuous outcomes will be summarised using means and standard deviations and analysed using *t* tests, analysis of covariance (ANCOVA), or multi-variate linear regression as appropriate. The analysis will be adjusted for baseline questionnaire score, stratification factor (study site), and other important prognostic factors if either ANCOVA or multi-variate linear regression is used. If the model assumptions are violated, the data will be summarised using medians and interquartile ranges, and either transformed to achieve normality prior to testing or, if this is not possible, tested using the Mann-Whitney *U* test.

Binary and categorical outcomes will be reported as proportions with 95% confidence intervals and will be assessed using chi-squared tests and logistic regression to adjust for potential confounders and baseline covariates. Ordinal logistic regression will be considered for ordered categorical outcomes.

Missing items will be dealt with using the pre-specified techniques each questionnaire recommends. If, for any questionnaire, no technique is pre-specified, mean imputation will be used if more than half the items are completed and the value regarded as missing otherwise. For key secondary outcomes (LLFDI frequency and limitation total domain scores, OKS, and KOOS) sensitivity analyses will be conducted on a PP basis to examine robustness of conclusions. Furthermore, missing data on the key secondary outcomes managed by complete case analysis will be investigated and MI conducted to see how sensitive the estimates are, if appropriate.

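### The 2-year analysis set is defined by providing 2-year data, not by reaching 2 years: eligible non-responders drop out, and the LLFDI model loses earlier data it could use

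*SAP article*

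**What the plan says.** Two sections of the SAP article define the 2-year group, and they differ.

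- Secondary outcomes, on data collection: "For the subgroup of patients who reach 2 years post-randomisation prior to the end of the trial, questionnaire data will be collected at this time". Membership depends on randomisation date and the end of the trial.
- Additional analyses, on the analysis: "For the subgroup of patients who provide 2 year follow-up data, methods previously described to analyse the data from each questionnaire will be repeated", with the 2-year measurement incorporated. Membership depends on having supplied a 2-year questionnaire.

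General analysis principles makes all randomised participants the default set, but with a proviso: "all analyses will be conducted for this population if not otherwise stated". Additional analyses does state otherwise.

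The methods to be repeated depend on the questionnaire.

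- LLFDI overall function: "linear mixed effects model with repeated measures incorporating outcome measurements at 6 and 12 months and adjusting for baseline score and study site as covariates", with a group-by-time interaction and multiple imputation (MI) for missing data.
- LLFDI frequency and limitation: "The LLFDI frequency and limitation total domain scores will be analysed using the methods described for the primary outcome".
- The other continuous outcomes, which at 2 years are OKS, KOOS quality of life, PASE and EQ-5D-5L: "analysed using *t* tests, analysis of covariance (ANCOVA), or multi-variate linear regression as appropriate".

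**The concern.** Supplying a questionnaire at 2 years happens after randomisation. Participants are not blinded, and the 2-year data are self-reported, so return of the form could depend on recovery, and differently in the two arms. If it does, a comparison confined to those who returned it is biased.

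The plan guards against this at 12 months, where it imputes to stay consistent with intention to treat. If the 2-year set consists only of those who provide 2-year data, no wholly missing 2-year questionnaire remains for MI to address.

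The second issue is precision. A repeated-measures model can include a participant with 6- and 12-month scores and no 2-year score, and those scores inform the 2-year contrast. Restricting the three LLFDI analyses to providers gives that up.

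**Working it through.** **1. The plan's own figure.** The document states no figure for the 2-year analysis. Its 12-month sample size reproduces: 3 / 10.91 = 0.275; n per arm = 2(1.960 + 1.282)² / 0.275² = 278; 278 / 0.90 = 309; total 618, against 620 stated. Nothing here is in dispute.

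**2. Who is left out, and why.** Compared with all randomised participants, the providers-only set omits two groups.

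- *Not yet at 2 years.* Recruitment closed on 26 January 2018 and follow-up was expected to finish in January 2019 (Trial status). If that is the end of the trial, anyone randomised after about January 2017 cannot reach 2 years. This depends on the calendar and not on arm or outcome, so omitting them costs precision only.
- *Reached 2 years, did not respond.* This is the difference between *reach* and *provide*, and it is the only part that is post-randomisation selection.

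**3. Size.** The document gives no proportion reaching 2 years, no 2-year response rate and no between-visit correlations. All of these are assumed below. Each simulation compares a baseline-adjusted ANCOVA in providers only with an estimate that also uses every participant's 6- and 12-month scores.

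*Simulation A* (2,000 trials): half reach 2 years, about 85% of them respond, 12–24 month correlation 0.75, true effect 3 points.

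*Simulation B* (620 participants, 1,500 replicates per scenario): 25%, 50% or 75% reach 2 years, about 80% of them respond, correlation 0.6 between all visits, true effect 0.275 SD.

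Precision, as variance reduction = 1 − (SE all / SE providers)²:

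| Scenario | SE, providers only | SE, all randomised | Variance reduction |
|---|---|---|---|
| B, 25% reach | 0.142 SD | 0.132 SD | 14% |
| B, 50% reach | 0.102 SD | 0.096 SD | 11% |
| B, 75% reach | 0.084 SD | 0.080 SD | 9% |
| A, 50% reach | 1.18 points | 1.03 points | about 23% (variance ratio 0.77) |

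The higher assumed correlation in A probably explains most of its larger gain.

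Bias in the providers-only estimate:

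- *Response depends on the 12-month score in one arm only.* In B (logit slope 1 per SD) the estimate is 0.223–0.230 if that arm is control and 0.313–0.318 if it is the intervention arm, against a true 0.275. The bias is about 0.04–0.05 SD in either direction; at SD 10.91 that is 0.44–0.55, or about 0.5 points. In A, where low 12-month scorers in one arm fail to return the form, the estimate is 3.78 against 3, a bias of 0.78 points. The all-randomised estimates are 0.27–0.28 SD (B) and 2.99 points (A).
- *Response unrelated to outcome, or related equally in both arms (B).* The furthest estimate from 0.275 is 0.257, a bias of 0.018 SD, or about 0.2 points.

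The all-randomised estimates are close to the truth because non-response was generated from the observed 12-month score, that is, missing at random. They would not be protected if response depended on the unobserved 2-year score itself.

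**The case against.** *Provide* may be shorthand for the calendar group. The sentence says that the earlier methods will be repeated with the new measurement, and for the LLFDI scores those methods are a mixed model plus MI, which is close to the remedy proposed here. The article also condenses a fuller plan. This has force as a guess at intent. But the sentence defines an analysis set, the all-randomised default yields to it, and nothing else in the article says that non-responders stay in. Even on the generous reading the wording needs correcting.

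Non-response at 2 years is the ordinary missing-data problem of any visit, and the plan accepts complete-case analysis for key secondary outcomes with MI as a check. That is fair, but it supports treating 2-year non-response in the same way, not defining it out of the analysis set.

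Using participants not yet at 2 years predicts later recruits' outcomes from those of earlier ones. Recruitment began with a single-site pilot and ended with 14 sites, so the site mix may have changed. This stands: an analysis limited to the calendar-eligible group is defensible and belongs alongside as a check.

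A reader might infer more than the documents support:

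- *That the 2-year comparison as a whole is no longer between randomised groups.* Exclusion by randomisation date is unrelated to arm; only non-response among those eligible is selective.
- *That earlier data are lost for every questionnaire.* OKS, KOOS, PASE and EQ-5D-5L are planned with methods that would not use a non-provider's earlier scores unless MI were added, and the 6- and 12-month analyses keep everyone.
- *That bias is expected.* It becomes material in these simulations only when response depends on outcome differently by arm, and nothing in the document shows that it does.

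**Conclusion.** The point holds in a limited form. As written, the 2-year analysis set excludes participants who reached 2 years but did not respond, which is post-randomisation selection. For the three LLFDI scores it also drops 6- and 12-month data that the planned model could use. Exclusion of participants not yet at 2 years is administrative and affects precision only.

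On assumed inputs, using all randomised participants lowers the variance of the 2-year effect by roughly 9–23%. Bias is about 0.5–0.8 LLFDI points, against the plan's 3-point example difference, if response depends on the 12-month score in one arm only. It is at most about 0.02 SD if response is unrelated to outcome or related equally in both arms. None of these sizes can be derived from the document.

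The 2-year analysis is supportive. No stated figure changes, and the primary conclusion, which rests on the 12-month analysis, is unaffected. The correction is still worth making because it is specific and cheap.

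**What to change.** Amend Additional analyses as follows.

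1. Define 2-year eligibility by randomisation date, in line with the Secondary outcomes section.
2. For the three LLFDI scores, fit the planned mixed model to all randomised participants, with 24 months as a third level of time and the group-by-time interaction, and report the 24-month contrast. Do not impute visits that were administratively unreached; the plan itself says that MI is unsuitable when a large number of values is missing. Repeat the analysis in the calendar-eligible group as a check.
3. For OKS, KOOS, PASE and EQ-5D-5L, keep the planned method with the calendar-eligible group as the analysis set, and use MI that includes the 6- and 12-month scores for non-response.
4. Report the numbers eligible and responding at 2 years by arm. The loss-to-follow-up reporting names only 6 and 12 months. The planned tables of data availability run to the end of follow-up, but need the eligible number as denominator.

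The cost is a change of SAP wording and slightly more analysis work, with no new data. The 24-month contrast will rest on a missing-at-random assumption, which should be stated.

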## Discussion

The CORKA trial will provide data regarding the effects of a multi-component community-based rehabilitation programme on the outcomes of patients 12 months after knee replacement surgery, compared to those receiving usual care. This paper provides details of the planned statistical analyses for this trial and will help reduce the risks of outcome reporting bias and data-driven results [24]. This paper has been prepared in accordance with the published guidelines for the content of statistical analysis plans [25].

## Trial status

Recruitment for the trial closed on 26 January 2018. In total 621 patients from 14 study sites were recruited. Follow-up is currently ongoing and expected to finish in January 2019. The final analysis will be conducted thereafter.

## Abbreviations

CACE: Complier average causal effect
ITT: Intention-to-treat
KOOS: Knee injury and Osteoarthritis Outcome Score
LLFDI: Late Life Function and Disability Instrument
MAR: Missing at random
MI: Multiple imputation
OKS: Oxford Knee Score
PASE: Physical Activity Scale for the Elderly
PP: Per-protocol
PROM: Patient reported outcome measure
